### **3. STUDY DESIGN**

This is an intervention study with a before- and after design, with the intervention being a quality improvement as is mandated by the national guideline LSKA.

## 4. STUDY POPULATION

### 4.1 Population (base)

The base population is formed by patients that are or will be treated with antithrombotics admitted to the university medical center Erasmus MC Rotterdam and general teaching hospital Reinier de Graaf Ziekenhuis Delft.

The Erasmus MC is a 1320-bed university medical center based in Rotterdam, Netherlands. Het Reinier de Graaf Ziekenhuis is a general teaching hospital located in Delft, Netherlands and has 590 beds.

The study is carried out from 2015 to 2018.

### 4.2 Inclusion criteria

In order to be eligible to participate in this study, a subject must meet all of the following criteria:

- Patients that are or will be treated with antithrombotics in the Erasmus MC or in the Reinier de Graaf hospital.
- Informed consent (we will ask permission from the patients to collect community pharmacy and to fill out four questionnaires).
- Only the first hospital admission of a patient within the study period will be included (readmission is an endpoint).

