### 4.4 Sample size calculation

In studies major bleeding complications tend to occur in about 2-3% of all patients per year on antithrombotics, but in every day practice it seems this rate is at least 10%. Conservatively, we will presume a rate of 5%. Thrombotic events are estimated to occur in 3% of treated patients per year in studies. As trials form the ideal situation, we assume this is the rate we could achieve with the S-team and that the rate is 4% in the pre-intervention period. This results in a composite rate of 9% and we expect to decrease this to 2.5% bleeding events and 3% thrombotic events (composite 5.5%). With an alpha of 0.05 and power of 0.80 the required sample size will be 917 patients in the pre-intervention phase and 917 patients in the post-intervention phase. In order to account for drop-outs 1900 patients will be included.

In a (not yet published) study aiming at the development of a prediction rule for VKA-related International Normalized Ratio (INR) elevation from our Erasmus MC group 3800 patients using VKAs were included over 4 years. Thus within 9 months over 700 patients using VKAs will be admitted to the Erasmus MC alone. As we include another hospital and other antithrombotics as well, we expect that 9 months will be sufficient to recruit the required number of patients.

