### 8.3.1 Pre-intervention phase

During a 9-month period usual care is provided to patients. This means that antithrombotic therapy, related patient instructions and handover after discharge are carried out by the physicians responsible for the patient. Patients that are or will be treated with antithrombotics in the Erasmus MC and in the Reinier de Graaf hospital will be included with the help of a clinical rule. The criteria on which the clinical rule screens are the use of antithrombotic drugs which are listed in table 1 and the use of antidotes which are listed in table 2.

Table 1: Antithrombotic agents

| Group of antithrombotic agents (ATC code) | Antithrombotic agents (ATC code) |
|-------------------------------------------|----------------------------------|
| Vitamin K antagonists (B01AA)             | Phenprocoumon (B01AA04)          |
|                                           | Acenoucoumarol (B01AA07)         |
| Heparin group (B01AB)                     | Heparin (B01AB01)                |
|                                           | Antithrombin III (B01AB02)       |
|                                           | Dalteparin (B01AB04)             |
|                                           | Enoxaparin (B01AB05)             |
|                                           | Nadroparin (B01AB06)             |
|                                           | Danaparoid (B01AB09)             |
|                                           | Tinzaparin (B01AB10)             |
| Direct thrombin inhibitors (B01AE)        | Bivaluridin (B01AE06)            |
|                                           | Dabigatran etexilate (B01AE07)   |
| Direct factor Xa inhibitors (B01AF)       | Rivaroxaban (B01AF01)            |
|                                           | Apixaban (B01AF02)               |
| Other antithrombotic agents (B01AX)       | Fondaparinux (B01AX05)           |

Table 2: Antidotes

| Group of antihemorrhagics (ATC code) | Antihemorrhagics (ATC code)                                   |
|--------------------------------------|---------------------------------------------------------------|
| Amino acids (B02AA)                  | Tranexamic acid (B02AA02)                                     |
| Vitamin K (B02BA)                    | Phytomenadione (B02BA01)                                      |
| Fibrinogen (B02BB)                   | Fibrinogen, human (B02BB01)                                   |

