### ***Readmissions within 3 months after discharge***

Three months after hospitalization the patient receives a small questionnaire about the use of healthcare. The questionnaire asks for visits to the general practitioner or the hospital because of a bleeding or thrombotic event within 3 months after hospitalization.

The hospital information system is used to register readmissions and the reason for readmission of the patients in the same hospital. The patient's general practitioner is asked for readmissions in other hospitals. Only the patient's first hospital admission is included in the study period (readmissions are the secondary outcome measures).

It will take about 5 minutes to fill out the questionnaire.

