### **8.3.3 Post-intervention phase**

During a 9-month period the S-team is active. From the clinical rule patients with antithrombotics will be identified and presented to the S-team. The main tasks of the S-team will be:

- Drafting of local guidelines
- Monitoring of the medication by the hospital pharmacist/clinical pharmacologist focused on patients that are treated with antithrombotics
- Patient instructions
- Proper handover to either the Thrombosis Service or the general practitioner, and to the community pharmacist, at the moment of hospital discharge
- Educating physicians, nurses and hospital pharmacists
- Offering consultation for professionals in- and outside the hospital

During the post-intervention phase the same data are collected as during the pre-intervention phase.

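### Counting only a patient's first admission in the whole study period selects the two compared phases differently and can bias the before-after comparison

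*Protocol*

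**What the plan says.** The inclusion criteria (4.2) limit each patient to one admission: "Only the first hospital admission of a patient within the study period will be included (readmission is an endpoint"). The readmissions subsection of 8.3.1 repeats the limit: "Only the patient's first hospital admission is included in the study period". Neither place refers to a phase.

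Section 4.1 gives the calendar frame: "The study is carried out from 2015 to 2018". Section 8.3 divides the study into pre-intervention, implementation and post-intervention phases. Of the compared phases, 8.3.1 says "During a 9-month period usual care is provided to patients" and 8.3.3 says "During a 9-month period the S-team is active".

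Section 3 describes the design: "This is an intervention study with a before- and after design". No control group is described, and 8.2 marks randomisation as not applicable. Section 10.1 names interrupted time series analysis and univariate and multivariate logistic regression for the primary outcome, without an adjustment for earlier admissions. The case report form (Table 3) records comorbidity and readmissions after the index stay, but no count of admissions before it.

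**The concern.** The same two hospitals supply both phases, and some patients on antithrombotics will be admitted more than once between 2015 and 2018. Under a rule that runs over the whole study, such a patient is counted at the first eligible admission and never again. The pre-intervention phase accepts frequent admitters as they come, because nobody has been counted before it starts. By the post-intervention phase many of them are already used up. The two groups then differ in their propensity to be admitted, for a reason unrelated to the S-team.

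In a before-after study without controls, a difference in who is selected cannot be told apart from a difference in outcome. The stated reason for the rule, that readmission is an endpoint, requires a bar only during the patient's own 3-month follow-up.

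**Working it through.** **Inputs from the protocol (4.4).** Composite rate 9% before and 5.5% after (difference 3.5 points), alpha 0.05, power 0.80, 917 patients per phase.

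**The plan's own figure.** For two proportions, two-sided, with p̄ = 0.0725:
- 1.96·√(2·0.0725·0.9275) = 0.7188, and 0.8416·√(0.09·0.91 + 0.055·0.945) = 0.3079.
- n = (0.7188 + 0.3079)² / 0.035² = 860.5, or 861.
- With continuity correction, n = (860.5/4)·(1 + √(1 + 4/(860.5·0.035)))² = 916.8, or 917. The figure reproduces.

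**Readmission within 3 months, no S-team effect.** Assumptions not in the protocol: yearly admission rate λ follows a gamma distribution with shape 0.5 and mean 0.3; the implementation phase lasts 6 months; any earlier admission since study start bars a patient. Write L(s) = E[exp(−sλ)] = (1 + 0.6s)^(−0.5), with s in years.
- Pre-phase (first admission in months 0 to 9): [1 − L(0.75) − L(0.25) + L(1)] / [1 − L(0.75)] = (1 − 0.8305 − 0.9325 + 0.7906)/0.1695 = 16.3%.
- Post-phase (first admission in months 15 to 24): [L(1.25) − L(2) − L(1.5) + L(2.25)] / [L(1.25) − L(2)] = (0.7559 − 0.6742 − 0.7255 + 0.6523)/0.0817 = 10.5%.
- Rule restarted at the post-phase: the first expression applies to both phases, so 16.3% and 16.3%.

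Simulating the same model with shape 0.5 to 1, mean 0.3 to 0.6 admissions a year and an implementation phase of 3 to 12 months gives 12% to 26% before and 9% to 15% after. The size depends on the assumptions; the direction is the same throughout.

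**Primary composite, no S-team effect.** Let f be the share of otherwise eligible post-phase patients barred by earlier inclusion, and RR their event risk relative to the others. Both are assumed. If the rate in all eligible patients is 9%, those who remain have rate r = 0.09/(1 − f + f·RR). The chance of a significant result favouring the S-team is Φ((Δ − 1.96·SE₀)/SE₁), with Δ = 0.09 − r and SE₀ and SE₁ the pooled and unpooled standard errors at 917 per phase. For f = 20% and RR 2: r = 0.09/1.2 = 0.075, Δ = 0.015, SE₀ ≈ SE₁ ≈ 0.01285, and Φ((0.015 − 0.0252)/0.0128) = Φ(−0.79) = 21%.

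| f | RR | Post-phase rate | Spurious drop (points) | Share of 3.5 points | Chance of false benefit |
|---|---|---|---|---|---|
| 10% | 1.5 | 8.6% | 0.4 | 12% | 5% |
| 20% | 2 | 7.5% | 1.5 | 43% | 21% |
| 30% | 2 | 6.9% | 2.1 | 59% | 38% |
| any | 1 | 9.0% | 0 | 0% | 2.5% |
| 10–30% | 0.7 | 9.3–9.9% | −0.3 to −0.9 | reversed | 1.5–0.5% |

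**How plausible is f?** If only included patients are barred, enrolling 917 after losing a share f means at least 917·f/(1 − f) pre-phase patients came back and were eligible again: 102 (11%) at f = 10%, 229 (25%) at 20% and 393 (43%) at 30%. These are minimums. If the eligible pool is twice the sample, they double, and f = 30% would need 786 of 917 (86%). The 30% row is an extreme case.

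**The case against.** A reader might infer that the rule is certain to bias the primary result in favour of the S-team. The protocol does not support that. It gives no bleeding or thrombosis risk by admission frequency; with equal risk nothing happens, and with lower risk the bias reverses. A higher risk is plausible, since a patient readmitted for a pre-phase bleed or thrombosis is barred later, but it remains an assumption. This objection stands.

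A reader might also infer that only the post-phase loses repeat admitters. Depletion starts when the study opens, so it also produces a drift within the pre-phase. The interrupted time series in 10.1 may absorb part of that drift. The two-group logistic regression in the same section would not, except as far as recorded comorbidity, earlier medication and laboratory data stand in for admission history. The table above is for an unadjusted comparison and does not estimate what remains after adjustment.

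Third, the term for the study period is never defined against the phases, and elsewhere the protocol uses the word period for a single phase (4.4, 8.3.1, 8.3.3, 10.2). A per-phase reading would remove the problem. But neither statement of the rule says so, and 4.1 dates the whole study, so the text still has to be settled.

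Finally, one admission per patient has a legitimate purpose, since it keeps observations independent. That purpose can be met with clustered standard errors.

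**Conclusion.** The concern holds as a flaw in a stated selection rule: on its natural reading the two compared phases are selected differently, and nothing in the protocol clearly offsets this. It is most secure for readmission within 3 months, where the direction favours the S-team almost by construction, although the size rests on assumed admission rates. For the primary composite the rule can bias the comparison, probably towards the S-team if repeat admitters have a higher event risk. The illustrative range is a spurious drop of 0.4 to 1.5 points, with a 5% to 21% chance of a false benefit. That range rests on assumed overlap and relative risk and on an unadjusted comparison; it is a sensitivity range and not an estimate. The rule should be changed, but neither a certain direction for the primary endpoint nor a defect that by itself invalidates the study can be shown from the protocol.

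**What to change.** In 4.2 and in the readmissions subsection of 8.3.1, state that a patient's first eligible admission within each phase (pre-intervention and post-intervention) is included, and that admissions inside the patient's own 3-month follow-up are not new inclusions. Alternatively, apply an identical look-back before each phase. In 10.1, specify patient-clustered (robust or GEE) standard errors, because some patients would then appear in both phases.

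The cost is a few sentences, slight within-patient correlation, and renewed consent from repeat patients. Recruitment to the post-intervention phase becomes easier. Adjusting for prior admissions is a useful option but not essential; it needs a small addition to the case report form, which at present looks back three months for medication and laboratory data and does not count earlier admissions.

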### 4.3 Exclusion criteria

A potential subject who meets any of the following criteria will be excluded from participation in this study:

- No informed consent
- Patients admitted for one day
- Patients admitted to the Intensive Care Unit
- Patients treated with low molecular weight heparins monotherapy for thrombosis prophylaxis
- Patients enrolled in a clinical trial of antithrombotic therapy
- Patients treated with phytomenadione used for the prevention and treatment of vitamin K deficiency
- Patients treated during hospitalization with a single dose of the antithrombotic agents

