Studies on the effect of a multidisciplinary antithrombotic team are scarce. Antithrombotic services are described mainly as pharmacist-led antithrombotic services in US hospitals that are predominantly aimed at warfarin dosing. This differs from the Dutch situation, where Thrombosis Services with a medical leader are responsible. In only 4 of 25 respondents of a survey such an antithrombotic service was multidisciplinary. One article describes an expanded antithrombotic stewardship, including both NOAC treatment and facilitating care after hospital discharge. It concerned a US one center pharmacist-led stewardship and the study included only a small retrospective control group of 12 patients. The majority of results were described for 409 patients monitored after implementation of the program. Also, the transition after discharge included only 34 patients, with 30 of them on warfarin therapy. Interventions consisted of changes to a more appropriate antithrombotic according to guidelines and dosing corrections. The length of hospital stay was reduced by 1.5 days and cost savings were \$270320 in 1.5 years. Discharge patient education and knowledge of patients is described in a few studies, but again mostly on warfarin. Given the known effect of patient education on adherence, patient education will be much more important for the NOAC therapy in which monitoring cannot be used to verify adherence.

The (lack of) implementation of the LSKA, and the shifting responsibilities regarding NOACs need solutions aiming at safe use of antithrombotics. The intervention in the present study consists of the implementation of an S-team. An S-team can be made responsible for LSKA implementation, can act as an expert team that can be consulted both from in- and outside the hospital, can take care of adequate handovers of patients discharged from hospital, and can improve patient education. A properly informed patient will more likely use antithrombotics safely and adherently, resulting in less complications.

At present the effectiveness of a multidisciplinary antithrombotic team is unknown. Therefore, the main objective of this study is to determine the effect of a multidisciplinary antithrombotic team ('S-team') on the frequency of bleeding and thrombotic events in two Dutch hospitals.

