### Secondary Objective(s):

The following secondary objectives when a multidisciplinary antithrombotic team (S-team) is installed in the hospital are:

1. To determine the effect on frequency of bleeding events.
2. To determine the effect on frequency of thrombotic events.
3. To determine the effect on severity of bleeding complications.
4. To determine the effect on length of the hospital stay.
5. To determine the effect on percentage of (re)admissions caused by antithrombotic medication.
6. To determine the effect on quality of life, adherence by the patient to the therapy and quality of care (patient satisfaction with antithrombotic therapy).
7. To determine the effect on adherence to the hospital protocol.
8. To determine the effect on costs.
9. To determine the effect on all-cause mortality.
10. To determine the effect on percent time in therapeutic range of vitamin K antagonists.

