#### 8.1.2 Secondary study parameters/endpoints

- Proportion of patients with  $\geq 1$  bleeding (major bleeding and mild to moderate clinically relevant non-major bleeding) event from time to start with antithrombotic medication (or hospitalization) until 3 months after hospitalization.
- Proportion of patients with  $\geq 1$  thrombotic event from time to start with antithrombotic medication (or hospitalization) until 3 months after hospitalization.
- Severity of bleeding complication
- Length of hospital stay (LOS)
- Percentage of readmissions within 3 months after discharge
- Patient related outcomes (quality of life, adherence of patient to therapy and patient satisfaction with the quality of care of the antithrombotic therapy)
- Adherence to the hospital protocol
- Healthcare costs (labor costs versus costs for bleeding/thrombotic events (including use of antidotes))
- All-cause mortality
- Percent time in therapeutic range of vitamin K antagonists during hospitalization and 3 months after discharge.

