|                 | Overview of medication use three months after hospitalization (coded with ATC-code  )+                                                                                                                                                                                                                                                                                                                                                                                                                                                                                                                                        |

\*Obtained from medical record of the hospital information system

+Obtained from the community pharmacist and the Thrombosis Service

\$Obtained from the patient using questionnaire

^Obtained by sending a small questionnaire asking for visits to the general practitioner or hospital because of a bleeding or thrombotic event within 3 months after hospitalization.

***The primary outcome of the study is the proportion of patients with a composite endpoint consisting of  $\geq 1$  bleeding (major bleeding and mild to moderate clinical relevant non-major bleeding) or  $\geq 1$  thrombotic events during and 3 months after hospitalization.***

Patients treated with antithrombotics and/or antidotes in the Erasmus MC and in the Reinier de Graaf hospital will be included with the help of a clinical rule (table 1 and 2). The data from the medical record of the hospital information system is used to determine whether there is a bleeding (major bleeding and mild to moderate clinical relevant non-major bleeding) or thrombotic event in patients who are enrolled in the study.

After hospitalization data from community pharmacist, general practitioner and the Thrombosis Services are used. At discharge the patient will be asked to fill in a consent form. By signing the consent form, the patient gives permission to retrieve patient data from the community pharmacist, general practitioner and the Thrombosis Services.

Definition of terms:

The ISTH definitions of bleeding in patients are as follows:

- Major Bleeding in non-Surgical Patients
  - 1. Fatal bleeding, and/or
  - 2. Symptomatic bleeding in a critical area or organ, such as intracranial, intraspinal, intraocular, retroperitoneal, intra-articular or pericardial, or intramuscular with compartment syndrome, and/or

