### 11.4 Benefits and risks assessment, group relatedness

The study is an evaluation of a quality improvement measure. The benefit of this quality project may be the increase of the safety in patients who are using antithrombotic therapy. The study will take a total of approximately 15-20 minutes (time that represents the completion of the questionnaires) for the patient; all other data are collected by retrospective medical record screening. There are no components in this study that are related with possible adverse effects.

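### The exclusion of one-day admissions is not limited to planned ones, so it can select on the realised length of stay, which is itself a secondary endpoint, and can bias that comparison against a reduction

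*Protocol*

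**What the plan says.** Protocol section 4.3 lists among the exclusions "Patients admitted for one day". It does not restrict this to planned, elective or day-care admissions. The same list excludes "Patients treated during hospitalization with a single dose of the antithrombotic agents".

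Length of stay is an outcome. Secondary objective 4 in section 2 reads "To determine the effect on length of the hospital stay", and section 8.1.2 lists it among the secondary endpoints. Section 1 reports an earlier US programme in these terms: "The length of hospital stay was reduced by 1.5 days".

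On timing, section 8.3.1 states "At discharge the patient will be asked to fill in a consent form", and section 11.4 says that, apart from the questionnaires, "all other data are collected by retrospective medical record screening". Section 8.3.3 has the screening rule present patients to the S-team and adds "During the post-intervention phase the same data are collected as during the pre-intervention phase". Section 10.2 plans linear or logistic regression for the secondary outcomes.

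**The concern.** An entry criterion should rest on something the intervention cannot change. Here the criterion can be read as the realised stay. In the post-intervention phase a patient may be presented to the S-team, be discharged after one day, and only then be found ineligible.

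A patient who would stay two days under usual care counts in the pre-intervention phase. If a comparable patient goes home after one day under the S-team, that stay is not counted. Using the same filter in both phases does not cure this, because the filter acts on a variable that the intervention may alter. Regression on the included patients cannot recover stays that were never in the cohort.

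At stake is the answer to secondary objective 4: a true shortening could be understated, missed or shown with the wrong sign.

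**Working it through.** **The plan's own figures.** The protocol states no figure for length of stay. Its 917 per phase reproduces exactly for 9% versus 5.5% (two-sided alpha 0.05, power 0.80, continuity correction). It does not involve length of stay.

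**Direction.** Let Y0 be a patient's stay under usual care, Y1 the stay under the S-team, and c the cut-off for exclusion. Assume that the S-team lengthens no stay.

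- True effect: E[Y1 - Y0 | Y0 > c]
- Measured effect: E[Y1 | Y1 > c] - E[Y0 | Y0 > c]
- Let f be the share of patients with Y0 > c whose Y1 falls to c or below, m the mean Y1 of these patients, and M the mean Y1 of those who remain.
- Measured minus true = f x (M - m).

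This is zero if f = 0 and positive otherwise, so it works against a reduction.

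**One case by hand.** Assume whole-day stays from a lognormal with median 5 and log-SD 0.8, and every stay of two or more days one day shorter. One-day stays are 6.6% before and 19.3% after.

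- f = (0.193 - 0.066) / (1 - 0.066) = 0.136
- Mean of all stays: 5 x exp(0.8²/2) = 6.89 days. Among stays of two or more days: (6.886 - 0.066) / 0.934 = 7.30
- True mean after the cut: 7.30 - 1.00 = 6.30
- M = (6.30 - 0.136 x 1) / (1 - 0.136) = 7.14
- Measured effect: 7.14 - 7.30, about -0.17 day, against a true -1.00. Simulation gives -0.16.

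**Range, continuous stays.** Assumptions, none of them from the protocol: lognormal stays with median/mean 4/6, 5/7 and 6/9 days, where log-SD = sqrt(2 ln(mean/median)) = 0.90, 0.82 and 0.90. One day is read as at most 1, 1.5 or 2 days. Each scenario has 2,000,000 simulated stays. The uniform shift takes 1.5 days off every stay, with a floor of 0.5 day.

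| Median/mean | Cut-off | Excluded before | Excluded after 1.5-day shift | True | Measured | Kept, 20% cut | Kept, 10% cut |
|---|---|---|---|---|---|---|---|
| 4/6 | 1 | 6.2% | 30.0% | -1.42 | +0.06 | 87% | 87% |
| 4/6 | 1.5 | 13.8% | 37.4% | -1.48 | +0.23 | 77% | 77% |
| 4/6 | 2 | 22.0% | 44.0% | -1.50 | +0.32 | 68% | 69% |
| 5/7 | 1 | 2.5% | 19.8% | -1.45 | -0.34 | 93% | 93% |
| 5/7 | 1.5 | 7.1% | 26.6% | -1.48 | -0.12 | 84% | 85% |
| 5/7 | 2 | 13.2% | 33.1% | -1.50 | +0.03 | 76% | 77% |
| 6/9 | 1 | 2.3% | 16.6% | -1.46 | -0.24 | 94% | 94% |
| 6/9 | 1.5 | 6.2% | 22.1% | -1.49 | -0.02 | 87% | 87% |
| 6/9 | 2 | 11.1% | 27.5% | -1.50 | +0.12 | 80% | 81% |

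If the 1.5-day reduction is confined to stays over 4 days, no stay crosses the cut-off and the measured effect equals the true one in all nine rows.

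**Range, whole-day stays** (median 3, 5 or 7 days, log-SD 0.6 to 1.0):

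- A uniform 1-day cut is measured as -0.75 to +0.37 day.
- A uniform 1.5-day cut is measured as -1.01 (68% kept, at median 7 and log-SD 0.6) to +0.57 day.
- A 20% cut keeps 66-97% of the true effect.
- If only half of the two-day stays become one-day stays, a true change of -0.02 to -0.15 day is measured as +0.12 to +0.59 day.

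**The case against.** The wording in section 4.3 could simply mean day-care admissions. If so, and if it is applied at admission, the problem largely disappears. This reading is plausible, and the point is therefore that the criterion is open, not that it is certainly applied to the realised stay. Section 8.3.1 also has case report data collected during hospitalisation, so some patients may be screened before discharge. But enrolment is completed only with consent at discharge, and nothing fixes eligibility earlier.

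The protocol also does not say that it expects a shorter stay. Its hypothesis concerns efficacy and safety, objective 4 only asks for the effect, and section 4.4 assumes nothing about stay. The 1.5 days is background from a single-centre, pharmacist-led programme whose control group, as section 1 notes, had 12 patients. A mean reduction of that size need not be a uniform shift, and nothing in the S-team's listed tasks implies that already short stays lose a day. This objection stands and limits what can be said about size.

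A reader might infer three stronger things that the documents do not support:

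- That patients are deleted from one phase only. The exclusion applies in both phases; the issue is unequal exclusion.
- That bias is always present. There is none if no stay is shortened to one day.
- That the post-intervention cohort loses its lowest-risk patients, so that other endpoints shift against the S-team. The protocol says nothing on the risk of patients discharged after one day.

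**Conclusion.** The concern holds in a limited form. As worded, the criterion allows selection on a secondary endpoint after exposure. Provided the S-team lengthens no stay, the direction follows from the design: whenever some stays of two or more days become one-day stays, the comparison is biased against a reduction.

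The size cannot be fixed from the protocol. Under the assumptions above it runs from no bias (only longer stays shorten), through a loss of 6-32% of the effect (10-20% proportional cut, continuous stays), to an effect mostly lost or reversed (uniform 1.5-day shift, continuous stays). Longer and less dispersed stays lose less. The point concerns one unpowered secondary endpoint; the primary sample size calculation is unchanged, and no effect on the primary comparison is shown.

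**What to change.** In section 4.3, define the exclusion by admission type known at entry, that is, a planned one-day or day-care admission, and apply it identically in both phases. Keep unplanned admissions, and admissions planned for longer, in the length-of-stay analysis when discharge comes after one day.

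Where planned status cannot be read from the record, count the one-day admissions in each phase and include them in a sensitivity analysis of length of stay from the hospital information system. The case report form already has a field for the reason for exclusion, which can supply part of this count. The single-dose exclusion may remove some of the same patients, so tabulate it by phase in the same count.

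The cost is more than one line of text. Planned status is not listed in the case report form (Table 3) and would have to be extracted, emergency admissions need a stated rule, and some short stays that carry little information enter the cohort. Patients discharged after one day would also have to be asked for consent like the others.
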